#### Safety outcomes

2.5.3

1.AEs, which will be assessed in 2 ways: significant abnormality (below or above twice the normal reference range) in the results of routine blood, urine or stool examinations, liver or kidney function tests, or electrocardiogram; AEs reported by clinicians and patients.2.Severe AEs (SAEs), which are defined as AEs that are life-threatening or lead to admission to the intensive care unit, prolonged hospitalization, or physical or mental disability. Once an SAE occurs, the principal investigator will report it to the hospital institutional review board and submit the appropriate paperwork to the Food and Drug Administration, Department of Jiangxi Province, within 24 hours.3.Treatment-related AEs, which must meet all the following criteria: the AE has reasonable time causality with treatment administration; comorbidities and co-interventions are not related to the AE; the symptoms of the AE improved or recovered when treatment was stopped; and the causality can be explained by pharmacological, biological, or phenomenological mechanisms.4.Withdrawal owing to AEs.

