### Randomization and blinding

2.3

Patients who pass the eligibility assessment will be randomly and proportionally divided into four groups: Group A, B, C, and D. We generated a block randomization sequence using Microsoft Excel that was saved as enciphered data. For allocation concealment, we will adopt centralized random assignment. Independent researchers who do not participate in trial procedures other than the randomization process will recode the random sequence into continuous numbers and label the boxes of trial samples. Samples will be allocated sequentially to participants. In this way, no one will know the group into which the next participant will be assigned.

This trial will have 3 intervention periods: standard treatment period, maintenance treatment period, and recuperation treatment period. The standard treatment period will be open-label. During the maintenance and recuperation treatment period, the clinicians, patients, outcome assessors, and data collectors will be blinded in terms of the assignment of HGMX or placebo but the administration of rabeprazole will be open-label. Except in instances of a severe AE, all the participants, medical providers, data collectors, and outcome reviewers will strictly adhere to the blinded de∗sign until the trial has been completed. In addition, an independent committee will supervise the allocation concealment and blinding, and if blinding is violated, the corresponding patient will be excluded. Figure 1 gives an overview of the study design and procedures.

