### Data analysis

2.10

The primary outcome data will be analyzed using the intention-to-treat population, in which all patients will be maintained in their initial group assignment regardless of compliance and contamination, and missing data will be imputed using the last observation carried forward method. Meanwhile, we will also conduct a sensitivity analysis with the per-protocol population. The safety outcomes will be analyzed using a safety population including all participants who received treatment at least once. Mid-term and final data analyses will be performed at the end of week 52 and 104, respectively.

Normality will be detected using the Kolmogorov-Smirnov method. Normal continuous variables will be described using the mean and standard deviation and compared using a *t* test or analysis of variance. Non-normal continuous variables will be described using the median and interquartile range and analyzed with the Mann–Whitney *U* test. Categorical variables will be presented as the frequency and percentage and compared using Pearson *χ*^2^ test. The boundary of significance for the *P* value will be .05, which will be adjusted using the O’Brien & Fleming method for multiple comparisons.

According to our factorial design, we will explore whether there exists an interaction between HGMX and rabeprazole. If there are no significant interaction effects, we will compare the main effects of HGMX and rabeprazole. In addition, we will perform subgroup analysis stratified by type of PUD (GU vs. DU) and *H pylori* infection status (yes vs no). All statistical analyses will be conducted in Stata v14.0 software.

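### Section 2.5.3 requires improvement on stopping before an AE counts as treatment-related, which undercounts that outcome, and its SAE list omits death and new ward admission

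*Protocol article*

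**What the plan says.** Section 2.5.3 of the protocol article lists four safety outcomes: all AEs, SAEs, treatment-related AEs, and withdrawals because of AEs.

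- **All AEs** cover marked abnormalities in laboratory tests or the electrocardiogram, together with "AEs reported by clinicians and patients". No causality condition is attached.
- **SAEs** are AEs that are "life-threatening or lead to admission to the intensive care unit, prolonged hospitalization, or physical or mental disability". An SAE triggers a report to the hospital review board and the provincial authority within 24 hours.
- **Treatment-related AEs** are introduced by "Treatment-related AEs, which must meet all the following criteria". The criteria are plausible timing, no relation to comorbidities or co-interventions, a mechanism that can explain the event, and "the symptoms of the AE improved or recovered when treatment was stopped".

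Section 2.10 adds: "The safety outcomes will be analyzed using a safety population including all participants who received treatment at least once". Section 2.3 states: "This trial will have 3 intervention periods: standard treatment period, maintenance treatment period, and recuperation treatment period". By sections 2.4.1 to 2.4.4, weeks 1–2 contain only standard Western drugs, HGMX or placebo runs from week 3 to week 52, and all interventions then stop while follow-up continues to week 104.

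**The concern.** Response to stopping is useful evidence on causality. Here it is a compulsory condition, joined by a logical AND to three others. Several kinds of event cannot show such a response whatever their cause, and the most severe ones are among them. A second compulsory condition, that comorbidities and co-interventions are unrelated, removes events with a joint cause. That matters in a trial where two arms also take rabeprazole in weeks 3–6 and section 2.4.5 permits drugs for comorbidities.

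The Introduction hypothesises a favourable safety profile, and the Discussion makes safety part of the trial's main purpose. HGMX or placebo is taken for 4 + 46 = 50 weeks. If few related AEs are reported at the end, a reader could not tell whether the product or the definition produced that result.

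The SAE list raises a separate reporting question. A new admission to an ordinary ward is not listed, so the 24-hour duty need not start.

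**Working it through.** No figure in the article depends on these definitions, so there is none to reproduce. The main check sets the rules beside the treatment schedule.

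**1. Which AEs can meet the stopping criterion?**

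| AE, assumed truly caused by HGMX | Can it improve or recover when treatment is stopped? |
|---|---|
| Fatal | No |
| Irreversible | No |
| Resolved while HGMX continued | No; nothing was left to improve at the stop |
| Began after week 52 | No; treatment had already ended |
| Led to stopping, then improved | Yes |
| Still present at the planned stop after week 52, then improved | Yes; AEs are recorded at every follow-up visit, including week 104 (section 2.6) |

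Because all four criteria must hold, the first four rows are never counted as treatment-related. The share of related AEs falling in those rows is not given and cannot be derived from the article.

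**2. Which serious events are in the SAE list?** Life-threatening events, intensive-care admission, prolonged hospitalisation and disability are named. Death is not named, though most deaths would probably pass as life-threatening. A new admission outside intensive care is not named and has no evident substitute in the list.

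**3. Safety population (minor).** Section 2.3 says "Patients who pass the eligibility assessment will be randomly and proportionally divided into four groups", which appears to put randomisation before week 1. The standard period is called an intervention period, and HGMX or placebo starts only in week 3. Read literally, a patient lost in weeks 1–2 has received treatment but neither HGMX nor placebo.

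Let *f* be the share of the HGMX arms in the safety set who never took HGMX. Then: observed rate = true rate × (1 − *f*). The HGMX arms hold 2 × 90 = 180 patients (section 2.9). The values of *f* and the true rate of 5% are assumptions.

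| *f* | Unexposed, of 180 | Apparent rate |
|---|---|---|
| 2% | 3.6 | 0.05 × 0.98 = 4.9% |
| 5% | 9 | 0.05 × 0.95 = 4.75% |
| 10% | 18 | 0.05 × 0.90 = 4.5% |
| 15% | 27 | 0.05 × 0.85 = 4.25% |

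The last row puts the whole planned 15% drop-out into weeks 1–2, so it is an extreme case.

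**4. If AEs of weeks 1–2 were also counted in the HGMX–placebo contrast.** Assume 10% against 5% of patients have an AE from week 3 on (ratio 2.0), and an independent share *e* in both arms has one in weeks 1–2. Then: any-AE rate = 1 − (1 − later rate) × (1 − *e*).

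- *e* = 10%: 1 − 0.90 × 0.90 = 19% against 1 − 0.95 × 0.90 = 14.5%, ratio 1.31.
- *e* = 30%: 1 − 0.90 × 0.70 = 37% against 1 − 0.95 × 0.70 = 33.5%, ratio 1.10.

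This shows only what could happen. The article does not state when AE counting starts.

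**The case against.** A reader might infer that the safety rules as a whole hide harm from HGMX. The documents do not support that. The four-part rule governs one of four safety outcomes. All-cause AEs, SAEs and AE withdrawals carry no causality filter, HGMX is compared with a blinded placebo, and the same rules apply in every arm. An excess of harm could still show in those outcomes.

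Other parts of the defence also stand:

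- The stopping criterion asks for improvement or recovery, so full resolution is not needed.
- The planned stop after week 52 gives a continuing AE a chance to qualify. It would therefore be wrong to cap the detectable share at the proportion of patients who stop early because of the AE.
- The co-intervention criterion excludes events to which those factors are related, which is narrower than any conceivable contribution.
- Bleeding and perforation are a secondary outcome (section 2.5.2), and acute bleeding or perforation is a reason for withdrawal (section 2.7), so such an event would not vanish from the record.
- Section 2.10 leaves the word treatment undefined, the flow diagram is not shown, and a population definition is not an AE window. It cannot be asserted that the safety set will contain unexposed patients, or that AEs of weeks 1–2 will be attributed to HGMX.

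None of this answers the two core points. The compulsory stopping criterion and the SAE list are stated rules, and applying them as written gives an incomplete count. They are not details merely left to a fuller document.

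**Conclusion.** The point holds for the treatment-related AE outcome and for the SAE definition. Fatal and irreversible AEs, AEs that resolved under continued HGMX, and AEs starting after week 52 cannot be classed as treatment-related, so that outcome is undercounted. The amount is unknown. The SAE gap is clearest for a new ward admission; for death it is mainly one of wording.

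The safety-population issue is a clarification. On the literal reading, the relative understatement of the HGMX rate equals the unexposed share, which is likely to be small. Mixing in AEs from weeks 1–2 could blur the HGMX–placebo contrast more, but that rests on assumed rates and on an AE window that the article does not specify. The all-cause AE outcome remains free of the causality filter.

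**What to change.** 1. In section 2.5.3, replace the requirement that all criteria hold with a graded causality assessment (unrelated, possible, probable, definite), made under the existing HGMX/placebo blind. Treat response to stopping and absence of other causes as supporting evidence, and count possible or higher as related.
2. Add death and any inpatient admission to the SAE definition, so that the 24-hour report covers them.
3. State that the safety conclusion rests on all-cause AEs and SAEs by randomised arm, with treatment-related AEs as supporting information.
4. As a clarification in section 2.10, define the population for the HGMX–placebo safety comparison as patients with at least one dose of HGMX or placebo, count AEs from that dose, and list AEs of weeks 1–2 separately.

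The cost is a wording amendment and a causality field on the case report form. Recruitment began in July 2017 and ethics committees at 11 hospitals approved the protocol, so the amendment has to pass through them, and AEs already classified may need a second look. Reported related-AE and SAE counts will be somewhat higher. No treatment, visit or sample size changes.

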### Study visits

2.6

We will visit patients at baseline and at weeks 6, 12, 26, 52, and 104. In addition to the baseline measures of the outcomes, patients will undergo an eligibility assessment and provide demographic data, including gender, age, marital status, living situation, complications, medication history, and allergy history at baseline. During follow-up, we will examine ulcer histopathology at weeks 12 and 26; perform physical examinations, laboratory tests, and an electrocardiogram at weeks 12, 26, and 52; and examine *H pylori* infection and gastric function and perform gastroscopy at weeks 12, 26, 52, and 104. SQD symptoms, AEs, and concomitant treatments will be assessed or recorded at all follow-up visits. Table 2 gives an overview of the trial visits.

**Table 2 T2:**
[figure not shown]
Schedule of trial visits.

### Discontinuation and withdrawal

2.7

Anyone who reports any of the following conditions during follow-up will be classified as withdrawal, and the patient will discontinue the trial.

1.Acute recurrent ulcer (eg, acute bleeding and perforation).2.SQD symptoms constantly worsen and require other interventions.3.Patient took <80% of the prescribed dose or any prohibited drug.4.Withdrawal owing to AEs.5.Patient request for withdrawal.

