#### Recuperation treatment period (weeks 7 to 52)

2.4.3

All participants will enter the recuperation treatment period at the beginning of week 7. In this period, the doses of HGMX and placebo will remain unchanged (ie, 30 g b.i.d.) for all groups for a 46-week recuperation treatment. Rabeprazole will not be administered to the corresponding groups during this period.

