#### Co-interventions

2.4.5

If participants have comorbidities not specified in the exclusion criteria, they will be allowed to receive targeted therapy, such as oral hypoglycemic drugs and insulin for diabetes, hypotensive drugs for hypertension, and antiallergy drugs for asthma.

Medicines that may damage the gastrointestinal tract, such as NSAIDs, theophylline and potassium supplements, and those that have a similar effect as our treatment, such as other PPIs, bismuth, and other Chinese herbal medicines, are prohibited.

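### Section 2.7 takes patients out of the trial, not only off the trial product, for reasons that partly depend on outcome, so later data can be lost differently between arms

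*Protocol article*

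**What the plan says.** Section 2.7 (Discontinuation and withdrawal) of the protocol article states: "Anyone who reports any of the following conditions during follow-up will be classified as withdrawal, and the patient will discontinue the trial". Five items follow: (1) acute recurrent ulcer, such as bleeding or perforation; (2) SQD symptoms that keep worsening and need another intervention; (3) "Patient took <80% of the prescribed dose or any prohibited drug"; (4) withdrawal because of AEs; (5) the patient's own request.

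Section 2.4.5 (Co-interventions) defines the prohibited drugs. Besides drugs that may harm the gut, it covers "those that have a similar effect as our treatment, such as other PPIs, bismuth, and other Chinese herbal medicines, are prohibited". No exception is made for treating an ulcer, and no end date is given. For weeks 7 to 52, section 2.4.3 says: "Rabeprazole will not be administered to the corresponding groups during this period".

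Under section 2.6 (Study visits), follow-up visits are at weeks 6, 12, 26, 52 and 104. The trial will "perform gastroscopy at weeks 12, 26, 52, and 104", with *H pylori* and gastric function tests at the same visits. For histology, "we will examine ulcer histopathology at weeks 12 and 26". It will also "perform physical examinations, laboratory tests, and an electrocardiogram at weeks 12, 26, and 52". Finally, "SQD symptoms, AEs, and concomitant treatments will be assessed or recorded at all follow-up visits".

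Section 2.10 analyses the primary outcomes by assigned group, whatever the compliance or contamination, and fills missing values by last observation carried forward (LOCF). The Discussion assigns the assessments after week 12 to long-term effects.

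**The concern.** The rule ends participation for events that are themselves outcomes or consequences of outcomes. Items 1 and 2 depend on outcome on their face: one is a complication or recurrence, the other is deterioration on the SQD scale, which is a primary outcome. Item 3 can depend on outcome indirectly. The trial's gastroscopies can find unhealed or recurrent ulcers, the regimen contains no PPI from week 7, and treatment with another PPI or bismuth would meet the withdrawal condition.

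If HGMX affects healing, symptoms or recurrence, the proportion leaving can differ between arms, and so can the missing data. At stake are later SQD scores and the week 26 histopathology (both primary outcomes), and recurrence, bleeding, perforation and AEs at later visits.

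**Working it through.** **1. Does the rule stop the product or end follow-up?** Section 2.4.4 on the extension period separates the two: interventions stop while follow-up and outcome assessment go on. Section 2.7 does not. It classifies the patient as a withdrawal who leaves the trial, and nothing else in the article keeps withdrawn patients under observation. The natural reading is that visits end.

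**2. Does the analysis plan restore the data?** No. Section 2.10 keeps the patient in the assigned group, but section 2.7 makes non-compliance and contamination reasons to leave. The values that an analysis regardless of compliance needs are therefore not collected. Primary outcomes get LOCF; for the lost recurrence, complication and AE observations, nothing replaces what was not seen.

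**3. What does one departure cost?** Inputs from section 2.6: follow-up visits at weeks 6, 12, 26, 52, 104 (5 in all, each with SQD and AE assessment); gastroscopy at 12, 26, 52, 104 (4); histopathology at 12, 26 (2); laboratory tests and ECG at 12, 26, 52 (3). Loss = scheduled assessments after the last visit attended; weeks lost = 104 minus that visit's week.

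| Last visit attended | Visits, SQD, AE lost | Gastroscopies lost | Histopathology lost | Laboratory/ECG lost | Weeks lost |
|---|---|---|---|---|---|
| Week 6 | 4 of 5 | 4 of 4 | 2 of 2 | 3 of 3 | 104 − 6 = 98 |
| Week 12 | 3 of 5 | 3 of 4 | 1 of 2 | 2 of 3 | 104 − 12 = 92 |
| Week 26 | 2 of 5 | 2 of 4 | 0 of 2 | 1 of 3 | 104 − 26 = 78 |
| Week 52 | 1 of 5 | 1 of 4 | 0 of 2 | 0 of 3 | 104 − 52 = 52 |

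No gastroscopy is scheduled at week 6, so that row cannot follow from one; it applies to departures for symptoms, dosing, AEs or an acute event. For a prohibited drug, the week 52 row applies only if section 2.4.5 is read as covering the extension.

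**4. Is this a power problem?** No figure in the plan depends on the withdrawal rule, so this step only asks whether extra loss matters for size. With rates 0.85 and 0.65, two-sided α 0.05 (sidedness is my assumption), power 0.80 and pooled variance under the null:

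n = [1.96·√(2·0.75·0.25) + 0.842·√(0.85·0.15 + 0.65·0.35)]² / 0.20² = 72.4, so 73 per group; 73/0.85 = 86; 4 × 86 = 344.

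The stated 360 is not short of this. For the pooled HGMX comparison, 180 × 0.85 = 153 per side gives power 0.984. If the rule removed a further 5 to 15 percentage points (assumption), 180 × 0.80 = 144 down to 180 × 0.70 = 126 would remain, with power 0.978 to 0.960. The risk is bias, not power.

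**5. What happens to the total effective rate?** When a trial endoscopy prompts the departure, its rating is recorded and carried forward. Suppose a share w of failures is treated and leaves, and a share h of these would heal if followed. Carrying the failure forward keeps the planned difference of 0.85 − 0.65 = 0.20. Observed later values would give

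(0.85 + 0.15wh) − (0.65 + 0.35wh) = 0.20(1 − wh).

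With w = 0.25 and h = 0.5 this is 0.175; with w = 0.75 and h = 0.9 it is 0.065. All values of w and h are assumptions. The gap does not show that LOCF is biased here. The two figures answer different questions: success without rescue, and status whatever treatment followed.

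**The case against.** The strongest objection is that the prohibited-drug route is a chain of inferences. It needs an ulcer found at gastroscopy, a decision to treat it with drugs, and a regimen that section 2.4.5 prohibits. The article describes no rescue treatment, and re-treatment with rabeprazole alone is not expressly covered. This stands as a limit on how often that route is used. It does not touch items 1 and 2, which need no such chain.

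A reader might infer that all planned failures (15% and 35% under section 2.9) will be withdrawn. The documents do not support that. Section 2.5.1 counts ulcers healed only to H1 or H2 as effective, so these rates do not give the number needing treatment. A reader might also infer that the bias favours HGMX; no direction follows from the text.

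It can also be said that the total effective rate, which drives the sample size, is largely protected, and that counting a rescued patient as a failure is a legitimate choice. Both stand. Requiring observed post-rescue values as its main analysis would count a failure healed on non-trial PPI as effective.

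Finally, the full protocol may provide for follow-up after withdrawal. That lowers confidence, but it does not change what section 2.7 says.

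**Conclusion.** The point holds as a design weakness that should be fixed. As written, section 2.7 ends data collection for triggers that partly depend on outcome, and the intention-to-treat statement cannot recover visits that never took place. A departure after week 12 costs 3 of the 5 SQD and AE assessments, the week 26 histopathology and three gastroscopies. These are among the visits that the Discussion relies on for long-term effects.

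The conclusion rests on reading section 2.7 as ending visits, and on at least some patients meeting items 1 to 4. The number affected, the imbalance between arms and the direction of bias cannot be derived.

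A reader might go further and call the total effective rate invalid. The documents do not support this, because the endoscopy that prompts departure is recorded. That protection does not extend to patients who leave before week 12, who have no scheduled follow-up gastroscopy to carry forward.

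**What to change.** Amend section 2.7 as follows.

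- Items 1 to 4 are at most reasons to stop the trial product. Item 4 becomes stopping the product because of an AE, still counted in the safety outcome on AE withdrawals. Choice of treatment stays with the clinicians.
- Record the date, the reason and any rescue treatment.
- Continue the visits already scheduled to week 104 unless the patient withdraws consent.

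In section 2.10, use the observed later values for safety, complications, SQD scores and histopathology, with post-rescue values flagged, and carry values forward only for primary outcome visits actually missed. For the total effective rate, a patient rescued for an unhealed or recurrent ulcer may still be counted as non-effective, with the observed-value analysis as a sensitivity analysis.

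The cost is a protocol amendment, with ethics approvals held at 11 hospitals, and a matching sentence in section 2.10. No visit is added to the schedule, and concomitant treatments are already recorded at each follow-up visit. Patients who would now leave after week 12 would be asked for up to three more gastroscopies and one more histopathology examination while off product. Some later assessments will follow non-trial treatment and must be interpreted as such.

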#### Extension period (weeks 53 to 104)

2.4.4

This is an observational period. All the interventions will be stopped, but follow-ups and outcome assessments will continue.

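### The definition of a treatment-related AE requires improvement after stopping treatment, and the withdrawal rule does not secure that observation, so treatment-related AEs may be under-counted (minor)

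*Protocol article*

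**What the plan says.** Section 2.5.3 names four safety outcomes: AEs, severe AEs (SAEs), treatment-related AEs and withdrawals owing to AEs. The third has a conjunctive definition: "Treatment-related AEs, which must meet all the following criteria". There are four criteria: plausible timing, no explanation by comorbidities or co-interventions, an explainable mechanism, and that "the symptoms of the AE improved or recovered when treatment was stopped". The section gives no category for an event whose course after stopping is unknown.

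Section 2.7 lists five conditions, of which the fourth is withdrawal owing to AEs. A patient who meets any of them "will be classified as withdrawal, and the patient will discontinue the trial". The wording refers to the trial, not to study treatment.

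On observation, section 2.6 says that "SQD symptoms, AEs, and concomitant treatments will be assessed or recorded at all follow-up visits", and those visits are at weeks 6, 12, 26, 52 and 104. Section 2.5.3 also takes in "AEs reported by clinicians and patients", with no stated end at withdrawal. Section 2.10 analyses safety in everyone treated at least once.

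**The concern.** The definition turns on what happens after treatment stops, and it admits no exception. It therefore leaves out whole kinds of event that a safety reader would want classified, among them those that do not get better. The withdrawal rule then takes out of the trial the patients in whom the criterion would most often have to be observed: those who stop because of an AE.

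Treatment-related AEs are a named outcome, and a good safety profile is part of the hypothesis in the Introduction. The Introduction also relies on relatedness when it reports no AEs related to HGMX in three years of post-market monitoring. If the trial's count of related events is too low, HGMX looks safer on that measure than it is.

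**Working it through.** The protocol states no figure on this point, so there is none to reproduce. The check applies the definition in section 2.5.3 to each possible course of an AE and then asks whether sections 2.4, 2.6 and 2.7 secure the observation needed. It takes the criteria as written: one that is not shown to be met is not met.

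**Step 1. The definition alone, with the other three criteria assumed met.**

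| Course of the AE | Improvement after stopping shown? | Can be treatment-related? |
|---|---|---|
| Treatment stopped, event improves, improvement recorded | Yes | Yes |
| Treatment stopped, event improves, course not recorded | Not shown | No |
| Treatment stopped, event persists or is irreversible | No | No |
| Event is fatal | Cannot occur | No |
| Patient continues treatment | No stop to judge by | No, while treatment continues |

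Four of the five rows fail, and three of those four fail whatever section 2.7 says. The main restriction therefore lies in section 2.5.3. It can exclude the gravest events: an SAE that leaves a lasting disability would be counted as an SAE but could not be counted as related.

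**Step 2. What section 2.7 adds.** It bears on the second row. A patient whose AE ends treatment also leaves the trial, so no planned visit after that point is secured. Section 2.4.4 shows that the protocol can keep the two apart. For the extension period it says "All the interventions will be stopped, but follow-ups and outcome assessments will continue". Section 2.7 has no such wording.

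**Step 3. Patients who complete treatment.** HGMX or placebo is given in weeks 3 to 6 and then "for all groups for a 46-week recuperation treatment", which is 4 + 46 = 50 weeks, ending at week 52. The one planned AE-recording visit after that is week 104, which is 104 − 52 = 52 weeks later. Completers thus have a planned observation off HGMX or placebo. A patient withdrawn for an AE has none that the text secures.

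**Step 4. Direction and size.** On the literal reading, failing to learn the course can move an event out of the related class but not into it. The size needs the number of related AEs that end treatment and the share *u* of them with an unrecorded course. The document gives neither. Assume, for illustration only, 10 such events that would all improve. The number counted is 10 × (1 − *u*), which gives 10, 7.5, 5, 2.5 and 0 for *u* = 0%, 25%, 50%, 75% and 100%. The range runs from no loss to total loss, so the size remains unknown.

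**The case against.** The strongest reply is that loss occurs only if nobody learns how the AE developed after stopping, and no section says so. Section 2.7 does not forbid AE follow-up. Clinician and patient reports have no stated end at withdrawal, coordinators keep in contact with patients (section 2.8), and the clinician already knows of an AE that caused withdrawal. The full protocol or the standard operating procedures may require follow-up to resolution. A criterion about improvement after stopping may itself presuppose that someone looks. All of this stands, and it is why the under-count is only possible. It does not answer the first step: persistent, irreversible and fatal events, and events in patients who continue, fail the definition even with perfect follow-up. Both rules are printed, so this is not a complaint about missing detail.

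Three stronger readings are tempting and not supported:

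- A reader might infer that AE follow-up ends at withdrawal. The text says only that the patient discontinues the trial.
- A reader might measure the harm by the scheduled visits a withdrawn patient misses. One observation after stopping satisfies the criterion, so missed visits do not measure the under-count.
- A reader might infer from the plan to "perform physical examinations, laboratory tests, and an electrocardiogram at weeks 12, 26, and 52" that no scheduled test falls off treatment. That is so only for HGMX or placebo. Rabeprazole ends after week 6, and bismuth and the antibiotics after week 2, so all three time points fall after those drugs. The criterion also speaks of symptoms, which makes test schedules a weak basis for the point.

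It is also fair to say that section 2.5.3 has no explicit rule for an unknown course. Coding it as not related is the literal result of an all-criteria rule, not a stated default.

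**Conclusion.** The point holds and is minor. Section 2.5.3 excludes by definition several kinds of event that treatment could have caused, and section 2.7 makes the excluding criterion harder to observe in patients who stop because of an AE. The consequence is a possible under-count, of unknown size, of the absolute number of treatment-related AEs.

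It reaches one of four safety outcomes. Total AEs, SAEs and AE withdrawals do not depend on the stopping criterion and are still counted in all treated patients. The rule is the same for HGMX and placebo, and that assignment is blinded to clinicians and assessors in the maintenance and recuperation periods, so no between-arm bias is shown. The conclusion rests on reading the criteria literally. As to section 2.7, it also rests on the absence of a follow-up rule elsewhere that the article does not show. If such a rule exists, the part about section 2.7 falls away and the part about section 2.5.3 remains.

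**What to change.** In section 2.7, state that withdrawal owing to an AE ends study treatment but not safety follow-up, and that the event is followed until resolved or stable if the patient consents.

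In section 2.5.3, treat improvement after stopping as supporting evidence and not as a mandatory criterion. Report an event whose course after stopping is unknown or cannot be observed as 'relatedness not assessable', separately from events judged not related.

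The cost is a few extra follow-up contacts, one added category on the AE form and a small protocol amendment. Recruitment began in July 2017 and 11 hospital ethics committees approved the protocol, so the amendment carries some administrative work. Where the later course was not recorded for patients already withdrawn, the new category can be applied to the existing records.
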